### Inclusion and exclusion criteria

According to Rome IV Criteria, IBS is diagnosed based on recurrent abdominal pain, on average, at least one day per week in the last 3 months and associated with any two or more of followings. They are related to defecation, change in frequency of stool, or change in form (appearance) of stool. Meanwhile, diarrhea predominant is classified by loose (mushy) or watery stools > 25% and hard or lumpy stool < 25% of bowel movements [22].

The diagnostic criteria of LSSD pattern of TCM is in reference to the “Guiding Principles for Clinical Study of New Chinese Medicines” [23]. LSSD is diagnosed when all the main symptoms and signs and associating with two or more secondary symptoms and signs are fulfilled. The main symptoms and signs include abdominal pain and diarrhea (inducing or aggravating by emotional upset or stress), and changes with defecation. Secondary symptoms and signs include borborygmus and passing gas frequently, distention and fullness in chest and hypochondrium or frequent sighing, emotional depression or irritability, anorexia and abdominal bloating, and pale red tongue with white thin fur and string like pulse.

Participants age of 18–65 years will be included if they fulfill of the diagnosis criteria of IBS-D based on Rome IV criteria, and the diagnosis of LSSD pattern of TCM based on “Guiding Principles for Clinical Study of New Chinese Medicines”, together with written informed consent.

Participants will be excluded if they are constipation predominant, mixed or unsubtyped IBS, abnormal colonoscopy within 5 years (except for benign polypectomy or hemorrhoids), with severe diseases on the system of heart, lung, liver, and kidney which are diagnosed by TCM theory, concomitant diabetes, Glucose-6-Phosphate Dehydrogenase deficiency, unstable hypertension, malignant tumor or have undergone thyroid surgery or medication within a year, and with diseases on the Spleen-Stomach system or other diseases that affect the movement of Qi on the Spleen-Stomach system, which are diagnosed by TCM theory. Participants with current concomitant medication with effects on gastrointestinal function (e.g., anticholinergic drugs, calcium channel blockers, 5-HT3 receptor antagonists, antidiarrheal agents, antacids, prokinetic agents, antidepressants, anxiolytics and intestinal flora regulating drugs), medical history of gastrointestinal surgery (except for appendicitis surgery), serum levels of alanine transaminase (ALT), aspartate transaminase (AST), and creatinine (Cr) exceed 1.5 times of the reference limit, history of allergy in Chinese medicine, and medical history of neurological diseases or psychiatric disorders will also be excluded. Women in pregnancy or breast-feeding, or subjects currently participating in another clinical trial or taking IBS treatment drugs within 1 week are not eligible to be enrolled in this study.

During the study, participants may opt to withdraw at any time. Those who are lost to follow up or withdraw from the study after randomization will be treated as drop-out cases.

### Intervention

The Chinese medicine JCM-16021 is composed of seven herbs, namely*Rhizoma Atractylodis Macrocephalae* (Baizhu) 20 g, *Radix Paeoniae Lactiflorae* (Baishao) 15 g, *Cortex Magnoliae Officinalis* (Houpo) 10 g, *Semen coicis Lachryma-jobi* (Yiyiren) 20 g, *Polygonaceae* (Huotanmu) 20 g, *Fructus Terminaliae Chebulae* (Hezi) 10 g, *Rhizoma Corydalis Yanhusuo* (Yanhusuo) 15 g. These herbs are processed in granules form and will be packaged in a sachet of 8 g with aluminum foil composite film. Every 21 sachets will be packed in a transparent bag with label for 1-week course. The placebo is made from caramel (0.55%), sunset yellow (0.01%), tartrazine (0.06%), gardenia yellow (0.06%), aspartame (0.8%), sucrose octaacetate (0.02%), starch (49.25%), and dextrin (49.25%). The form, color, package, usage, and dosage of placebo is consistent with the Chinese medicine JCM-16021 granules, as is shown in Additional file 2. Participants will take either the Chinese medicine JCM-16021 granules or placebo granules (8 g/sachet) orally, one sachet each time, three times daily half an hour after a meal for 8 weeks.

All investigational medicinal product (IMP) including the Chinese medicine JCM-16021 granules and placebo are produced by the Purapharm (Nanning) Pharmaceutical Co. Ltd. The entire manufacturing process will be in strict compliance with the standards of Good Manufactory Practice (GMP). The production process of the Chinese medicine JCM-16021 granules and placebo granules will be compliant with the quality specification standards, respectively. According to the Chinese Pharmacopoeia (2015), all qualified IMP will be delivered to the site of clinical study and stored within a range of 25 ± 2 °C and relative humidity range of 60 ± 10% [24]. The investigators are responsible for ensuring adequate accountability of all used and unused IMP. For better guaranteeing the safety and quality of the Chinese medicine JCM-16021 granules, accelerated stability tests, heavy mental and toxic elements, pesticides residues, and microbial limit will be conducted.

### Primary outcome

The primary outcome is the improvement rate on the global assessment of improvement (GAI) score at week 10, same as the previous small scale study [16]. The participants will be asked to give a global assessment of their IBS symptoms at visit 3, 4 and 5 with the question “In the past 7 days, compared with your IBS symptoms before you started the trial, are you now: substantially worse, moderately worse, slightly worse, no change, slightly improved, moderately improved, or substantially improved? [25]’’ The global symptom improvement will be evaluated by scales (substantially worse = 0, moderately worse = 1, slightly worse = 2, no change = 3, slightly improved = 4, moderately improved = 5, substantially improved = 6). The 0–2 score, 3 score and 4–6 score represent worsen, no change and improvement, respectively. Improvement rate of GAI is defined as the proportion of participants with improvement (in scores of 4 or greater).

### Secondary outcomes

#### IBS symptoms

IBS symptoms, including abdominal pain (with scores from 0 to 10 representing none to most severe), stool frequency and stool consistency will be recorded by participants in a diary throughout 18 weeks of study. Investigators will grade each symptom by cardinal symptoms evaluation quantitation scale (None = 0, Mild = 1, Moderate = 2, Severe = 3) shown in Additional file 3: Table S1. The changes of these IBS symptoms before and after the treatment will be used for efficacy evaluation. The details are as below:i.Pain responder rate in daily worst abdominal pain scores: According to the guidance of the U.S. FDA, pain responder is defined as that participant who meets the daily pain response criteria for at least 50% of the days with diary entries during the observational period of interest. Daily pain response is defined as the ≥ 30% decrease in the worst abdominal pain scores in the past 24 h compared to baseline (average of daily worst abdominal pain the 2-week prior to randomization). Pain score is ranked from 0 to 10 representing none to the most severe [26].ii.Stool consistency responder rate in daily stool consistency scores: Stool consistency responder is defined as that participant who meets daily stool consistency response criterion (i.e., score of 1, 2, 3, or 4 or absence of bowel movement if accompanied by ≥ 30% decrease in worst abdominal pain scores compared to baseline pain) for at least 50% of days with diary entries during the observational period of interest. Bristol stool scale is defined as 7-point Scale in which a score of 1 = separate hard lumps, 2 = sausage shaped but lumpy, 3 = sausage-like with cracks on the surface, 4 = sausage-like but smooth and soft, 5 = soft blobs with clear cut edges, 6 = fluffy pieces with ragged edges, and 7 = watery with no solid pieces [26].iii.Improvement rate and efficacy rate*:* The standards of efficacy assessment of single symptom are as follows: (a) Excellent: symptoms disappearing; (b) Effective: symptom score decreased ≥ 2 points; (c) Helpful: symptom score decreased 1 point; (d) Invalid: no change in symptom score. Improvement rate is defined as the proportion of participants in excellent, effective and helpful. Comprehensive efficacy judgement standard of cardinal symptoms is calculated by “(total scoring of prior treatment − total scoring of post treatment)/total scoring of prior treatment × 100%”. Clinical remission is defined as symptom disappearing, symptom improvement (≥ 80%), helpful (between 50 and 80%), invalid (< 50%). Total effective rate is defined as the proportion of participants with clinical remission and symptom improvement [23].

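### The daily pain-responder rule classes participants with unchanged pain on about three or fewer days a week as responders, which raises both arms' rates and dilutes this secondary comparison

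*Protocol article*

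**What the plan says.** The IBS symptoms section of the protocol article, under secondary outcomes, lists the pain responder rate first and attributes its definition to regulatory guidance. Its parts are:

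- **Daily criterion:** a "30% decrease in the worst abdominal pain scores in the past" 24 hours, of at least that size, relative to baseline.
- **Baseline:** the "average of daily worst abdominal pain the 2-week prior to randomization". Nothing limits this average to days with pain.
- **Participant criterion:** a "pain responder is defined as that participant who meets the daily pain response criteria for at least 50% of the days with diary entries" in the observation period.
- **Scale:** "Pain score is ranked from 0 to 10 representing none to the most severe", so a pain-free day scores 0.

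The stool-consistency responder rule in the same section reuses the pain criterion. A day without a bowel movement counts as a response if there is the same 30% "decrease in worst abdominal pain scores compared to baseline pain".

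The section on inclusion and exclusion criteria takes the diagnosis from Rome IV, which asks for "recurrent abdominal pain, on average, at least one day per week in the last 3 months". The other inclusion conditions are age, the TCM pattern and consent. Neither that section nor the registration table sets a minimum pain score or a pain threshold in the run-in.

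**The concern.** The rule sets a single day against a mean. For a participant whose pain comes and goes, the run-in mean lies between the pain-free days and the pain days. Each pain-free day is then far below the baseline even if nothing has changed, and a participant who is pain-free on more than half of the days passes the 50% threshold automatically. The eligibility criteria admit such participants.

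Automatic responders respond in both arms alike. They lift both responder rates and carry no information about treatment, so the difference between arms shrinks. A reader would also take a high responder rate as pain relief when part of it is the ordinary rhythm of the condition. The same weakness passes to the days without a bowel movement in the stool-consistency rule.

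**Working it through.** The article gives no numerical result or power for this endpoint, so there is no stated figure to reproduce. The check applies the rule as written to participants with no change.

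**1. Exact arithmetic, fixed weekly pattern.** Let a participant have pain of score s on k days a week and 0 on the others, in run-in and treatment alike. The baseline is s × k/7. A day is a response if its score is at most 0.70 × baseline.

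- Pain-free day: 0 is at most 0.70 × s × k/7, so it is always a response.
- Pain day: s is at most 0.70 × s × k/7 only if k is at least 10, so it is never a response.
- Share of response days: (7 − k)/7, whatever the score s.

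| Pain days a week | Response days | Responder with no change? |
|---|---|---|
| 1 | 6/7 = 85.7% | yes |
| 2 | 5/7 = 71.4% | yes |
| 3 | 4/7 = 57.1% | yes |
| 4 | 3/7 = 42.9% | no |
| 5 | 2/7 = 28.6% | no |
| 7 | 0% | no |

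Example at the eligibility minimum: a score of 7 on one day a week gives a baseline of 7/7 = 1.0. Six of seven days score 0, so this participant is a responder.

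**2. Simulation with day-to-day variation, no change.** Each day is a pain day with probability k/7, over 14 run-in days and 56 treatment days. The score distributions on pain days are assumptions. Rates are among participants with a non-zero run-in mean.

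| Pain days a week | Scores about N(5, 1.5) | Scores uniform 3 to 8 |
|---|---|---|
| 1 | 100% | 100% |
| 2 | 100% | 100% |
| 3 | about 91% | 89% |
| 4 | 26% | 22% |
| 5 | under 2% | about 4% |
| 7 | about 0.2% | 0.2% |

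If every pain day is made 2 points worse under the normal model, the rates are still 100%, 100% and 89% at one, two and three pain days a week. For these participants the endpoint hardly registers pain intensity.

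**3. Zero baseline.** At one pain day a week, the chance of no pain day in 14 run-in days is (6/7)^14 = 0.116, about 12%. The percentage decrease is then 0/0.

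**4. Illustration of dilution.** If a share f responds automatically in both arms, each rate p becomes f + (1 − f)p, and the difference is multiplied by (1 − f). Assume 35% v 50% among the others and 166 per arm:

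- f = 0: 35% v 50%, 15 points, power 79%.
- f = 20%: 0.20 + 0.80 × 0.35 = 48% v 0.20 + 0.80 × 0.50 = 60%, 12 points, power 59%.
- f = 40%: 0.40 + 0.60 × 0.35 = 61% v 0.40 + 0.60 × 0.50 = 70%, 9 points, power 41%.

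The 35%, the 50% and f are assumptions. The 15 points and 166 per arm are borrowed from the sample size for the GAI.

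**5. Would a baseline floor cure it?** No. A score of 10 on three days a week gives a run-in mean of 30/7 = 4.29 and still 4/7 response days. Changing to a 30% drop in the mean and requiring a run-in mean of at least 3 also fails. Under the normal model, unchanged participants who pass the floor are responders in 67% of cases at three pain days a week and 20% at four. Selecting on a noisy 14-day mean brings regression to the mean. Without the floor, the average-based responder still gives 33%, 22% and 15% at one, two and three pain days a week.

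**The case against.** **One day a week is a diagnostic minimum, not the typical pain frequency.** This stands. The documents give no distribution of pain days, so the affected share may be small. A reader might infer that the rule makes a responder of anyone whose pain is unchanged. It does not: someone with steady daily pain is classified correctly, and the effect is small from five pain days a week. Widely varying daily pain is an exception: 6 on three days and 2 on four gives a mean of 26/7 = 3.71, a cut-off of 2.6 and 4/7 response days.

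**It cannot create a false treatment effect.** This also stands. With no treatment effect, the rule acts alike in two randomised, blinded arms. The harm is inflated rates and a weaker contrast, not bias towards the herbal product.

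**The power loss is hypothetical.** Correct. No power is claimed for pain response, so the figures show only how dilution works.

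**The definition follows regulatory guidance.** The article says so, and this cannot be checked here. The attribution does not alter what the rule does under this protocol's entry criteria.

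**The plan already covers it.** In part. The statistical analysis section analyses change from baseline with baseline as a covariate for repeated measures, and IBS-SSS captures severity and frequency of pain. Mean daily pain is not named, however. The zero-baseline case may be settled in the SAP, which is not shown, but the responder definition itself is stated in the article.

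**Conclusion.** The point holds as a defect of a stated secondary endpoint. Participants with an unchanged pattern of pain on about three or fewer days a week are classed as responders. For a fixed weekly pattern this follows from the wording alone, with no assumption about scores. The simulated rates rest on the assumed score distributions, and the two tried agree closely. At four pain days a week about a quarter are misclassified; at five, under 2% to about 4%, depending on the distribution.

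The consequence is higher responder rates in both arms and a diluted difference, here and on the no-bowel-movement days of the stool-consistency rule. Its size depends on the share of participants with infrequent pain, which only the diaries can show. The documents support neither the inference that the trial's main conclusion is at risk nor that this endpoint is useless for the whole sample. The primary GAI outcome does not use the rule, and participants with pain on most days are generally classified properly.

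**What to change.** Set the following before unblinding:

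1. Make the main pain analysis an ANCOVA of mean daily worst pain over the stated treatment window, with the run-in mean and centre as covariates, in all randomised participants. Apply no baseline floor. This compares means with means and does not drop participants with infrequent pain.
2. Keep the daily-rule responder rate as published, but label it supportive.
3. Report beside it, by arm, the share of participants and of run-in days that already meet the rule during run-in. This shows how much of the rate is automatic.
4. State that a run-in mean of 0 cannot count as a pain response, and apply the same statement to days without a bowel movement in the stool-consistency rule.

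The cost is some wording and programming on diary data already collected. The trial status section says follow-up is complete, so the responder rate would lose prominence after data collection. The blinding section keeps the code confidential until the final analysis and report are complete. The change can therefore still be made blind, and it should be dated and documented as such.

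### The stool-consistency responder rule has no stool baseline, so some eligible participants can count as responders without any change in stool form

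*Protocol article*

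**What the plan says.** The protocol article, Secondary outcomes, IBS symptoms, item (ii), defines a daily stool response as a "score of 1, 2, 3, or 4 or absence of bowel movement if accompanied by ≥ 30% decrease in worst abdominal pain scores". The reference for that decrease is the participant's pain at baseline, not stool form. A responder meets this "for at least 50% of days with diary entries during the observational period of interest". The scale is spelled out in the same item: "1 = separate hard lumps, 2 = sausage shaped but lumpy" lie inside the success range, and "5 = soft blobs with clear cut edges" lies outside it.

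Item (i), the pain responder, is built differently. Each day's pain is "compared to baseline (average of daily worst abdominal pain the 2-week prior to randomization"). The paragraph that introduces these items says that symptom changes from before to after treatment serve to evaluate efficacy.

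Under Inclusion and exclusion criteria, the only stool requirement for the diarrhea subtype is "loose (mushy) or watery stools > 25% and hard or lumpy stool < 25% of bowel movements". Neither that section nor the visit schedule in Methods/design sets a minimum number of loose-stool days during the two-week run-in.

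**The concern.** Item (ii) measures a state during treatment, not a change from run-in. The one baseline it names is for pain and, on the natural reading, applies only to days without a bowel movement. The entry floor for loose stools (above 25% of movements) lies below the share of failing days that a responder may have (up to 50%). A participant can therefore be eligible and already satisfy the success rule before the first dose. That conflicts with the section's own statement that before-after changes are used.

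Participants who respond unchanged carry no information about treatment. They raise the reported response rate in each arm and shrink the difference between arms. A reader of the results could not tell what share of the stool responders had improved.

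A lesser matter is that types 1 and 2 count as success, although the entry criteria cap hard or lumpy stool at under 25% of movements. A shift towards hard stools would not be visible in this rate.

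**Working it through.** The article states no rate, difference or power for this endpoint, so there is no figure of the plan to reproduce. The 166 per group, 80% power and 15-point difference under Sample size calculation belong to the primary outcome and are not used here.

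**Inputs from the article.** Success scores are 1-4; the responder threshold is 50% of diary days; loose or watery stools exceed 25% of movements at entry; treatment lasts 8 weeks, taken as 8 × 7 = 56 diary days.

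**Assumptions.** Days are independent, all 56 have an entry, and stool pattern does not change from run-in. Let q be the daily chance of meeting the criterion. The chance of being an unchanged responder is P(X ≥ 28), with X ~ Binomial(56, q).

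**Step 1. Most favourable case for the concern:** one score a day, every non-loose day scored 1-4, so q = 1 − share of loose days.

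| Loose days | q | P(responder, unchanged) |
|---|---|---|
| 26% | 0.74 | about 1.00 |
| 30% | 0.70 | 0.999 |
| 40% | 0.60 | 0.95 |
| 45% | 0.55 | 0.81 |
| 50% | 0.50 | 0.55 |
| 60% | 0.40 | 0.08 |

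**Step 2. Other failing days.** Type-5 days fail, and so do days without a bowel movement unless pain is at least 30% below baseline. If these make up a further 20% of days, q = 1 − loose share − 0.20:

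- 26% loose: q = 0.54, P = 0.77
- 30% loose: q = 0.50, P = 0.55
- 40% loose: q = 0.40, P = 0.08

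**Step 3. Movements against days.** Entry counts bowel movements and the rule counts days. The article does not say which stool is scored on a day with several. Suppose the worst is scored, stools within a day are independent, 30% of movements are loose and the rest score 1-4. With m stools a day, q = 0.70^m:

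- m = 1: q = 0.70, P = 0.999
- m = 2: q = 0.49, P = 0.49
- m = 3: q = 0.343, P = 0.01

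The answer for an eligible participant therefore runs from near certainty to near zero, depending on facts that the article does not give.

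**Step 4. Effect on the comparison.** If a share f of each arm responds unchanged and the rest respond at p0 and p1, the observed difference is [f + (1 − f)p1] − [f + (1 − f)p0] = (1 − f)(p1 − p0). With illustrative rates of 25% and 40% among the rest:

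| f | Control | Active | Difference |
|---|---|---|---|
| 0 | 25.0% | 40.0% | 15.0 points |
| 10% | 32.5% | 46.0% | 13.5 points |
| 20% | 40.0% | 52.0% | 12.0 points |
| 30% | 47.5% | 58.0% | 10.5 points |

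The values of f, p0 and p1 are chosen only to show the mechanism; none comes from the article.

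**The case against.** The strongest reply is that an absolute threshold is a legitimate responder definition. The article cites a source for it and links that source to regulatory guidance in item (i). Change in stool consistency is also measured elsewhere: item (iii) classes each symptom, graded 0-3, by its before-after decrease. Both points stand. The aim of improving stool consistency does not rest on item (ii) alone. But neither point cures the pairing of this threshold with an entry floor that lies below it, and the article itself fixes the rule.

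A reader might infer more than the text supports:

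- *Everyone with loose stools on fewer than half of days is a responder.* Steps 2 and 3 show otherwise. At least half of all diary days must meet the criterion, so the most that can be said is that such a participant can be one.
- *There is no baseline at all.* Baseline pain is named. If its clause were read as governing scores 1-4 as well, an unchanged participant would generally not respond. The natural reading is narrower, but the wording should settle it.
- *A participant driven into constipation always responds.* Days without a bowel movement need the pain decrease, and new symptoms are recorded as adverse events. The narrower point about types 1-2 stands. Whether to restrict success to types 3-4 is a debatable trade-off.
- *The trial loses a stated amount of power.* No power is claimed for this endpoint. Borrowing the primary outcome's figures would mislead.
- *The result is biased towards the active arm.* Randomization makes unchanged responders equally likely in each arm, so the effect is dilution.

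Recruitment and follow-up are complete, which argues for adding an analysis, not replacing the definition.

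**Conclusion.** The point holds in a limited form. Item (ii) lacks a stool comparison with run-in, and together with the entry floor above 25% of movements it allows some eligible participants to be responders with no change. That contradicts the section's statement that before-after changes are used. How many are affected cannot be derived from the article. The individual chances of 0.999 to 0.01 at 30% loose movements rest on independent days, one stool-scoring convention and assumed stool counts. The consequence is an inflated rate in both arms and a difference shrunk by the factor (1 − f) on one secondary endpoint. The primary outcome is untouched.

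**What to change.** Specify the following before unblinding, using the run-in and treatment diaries already collected:

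1. Add a run-in comparator to the stool responder analysis. Choose one and name it in advance: (a) count as responders only participants who did not already meet the criterion on at least half of run-in days; (b) analyse the reduction in loose-stool days from run-in; or (c) adjust for the run-in share of response days. All three use pre-randomization information, so they keep the comparison between arms fair.
2. Report by arm how many participants met the rule during run-in. This supplies the f that the article does not give.
3. State that the pain clause applies only to days without a bowel movement.
4. Report the proportion of type 1-2 days by arm, so that a shift to hard stools is visible.
5. Keep the 1-4 rule as written alongside, for comparability with other trials.

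The cost is one added, labelled analysis and two descriptive lines, with no new data. Under option (a) the reported response rate will be lower or unchanged in both arms.
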